#### HCF:

We anticipate 300 workers from 6 facilities. Assuming the minimum number of 30 workers in each facility and ICC of 0.01, a design effect of 1.36 is expected. We anticipate 96% and 84% powers to detect the medium effect sizes of 0.5 and 0.4 for the difference in outcomes between the two interventions. We expect the proposed sample sizes of YGBMSM and HCWs to be enough to detect the medium effect sizes of the intervention.

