**Methodology:**

We will employ the ADAPTT-IT framework to adapt LAFIYA and evaluate its feasibility and effectiveness in addressing intersectional stigma and increasing HPART uptake among YGBMSM residing in Ghanaian slums. In aim 1, we will hold focus groups (n=5) and interviews (n=20) among YGBMSM and two FGDs among GBMSM-led organizations. At the HCF level, we will hold 6 FGDs and interviews (n=20) among nurses. In AIM 2, we will randomly assign 6 healthcare facilities (HCFs) to receive the LAFIYA (n=3) or wait-list control (n=3). Friend groups (cluster) of YGBMSM (N=240) will be assigned to receive LAFIYA (n=120) or a wait-list control (n=120). We will collect 3-, 6-, and 9-months post-intervention data among YGBMSM(n=240) and HCWs(n=300) to measure HPART adherence (primary outcomes), ISD reduction, HIV and status-neutral knowledge (secondary outcomes), and intervention acceptability, appropriateness, and feasibility (implementation outcomes).

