#### Randomization.

We will assign 3 HCFs to intervention or control groups based on size; we will first stratify 6 HCFs into groups of two, larger, medium, and smaller sizes, and assign one from each stratum to either arm using SRS.

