#### Data analysis.

We will use the intent-to-treat (ITT) technique to analyze data. We considered other methods (e.g., per protocol approach), but ITT is less biased since all participants are assessed whether they received the intervention or not. Data collected will be exported to Stata for cleaning and further analysis. Using the Monte Carlo Markov Chain approach based on a multivariate normal distribution of items, we will assess missing patterns in the instrument and impute missing responses with at least 70% of responses. Instruments scores will be calculated with observed and imputed responses. We will summarize the characteristics of participants and calculate Cronbach’s alpha to check internal reliability within scales. We will calculate a mean with a confidence interval for the variables and proportions of responses to the primary and secondary outcome variables. Variables with skewed distribution will be considered for being log-transformed or categorized in ordinal form. We will run inferential statistics such as paired t-test to compare pre-and post-means, McNamara’s test to compare pre-and post-proportions, and correlation analysis to examine the relationship between variables. We will also develop longitudinal models of the outcomes repeatedly measured at baseline, 3, 6, and 9 months post-intervention using a generalized linear mixed effect model (GLMM) with random intercept and peer group, which incorporate ICCs. The GLMM will include time-group interaction to estimate the intervention effect and pre-post changes. The GLMM will consist of all completed observations and drop-outs observed at least once post-intervention. Thus, we will not miss any individuals unless they are entirely missing at all post-intervention periods. Residuals will be assessed for normality assumption and influential outliers diagnosed with leverage, Cook’s distance, and DFFIT. The GLMM will be replaced with logistic and Poisson regressions with random effects when an outcome is binary and count data. We will repeat the same models separately for each site and compare the effect sizes between the sites. When we find any demographics, which are not equivalent between the two interventions, they will be included in the model as covariates. Acceptability, feasibility, and appropriateness will be evaluated with descriptive statistics of the implementation outcomes. **The process defined in AIM**1 will be used to analyze the follow-up qualitative data.

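### The healthcare-worker design effect of 1.36 does not follow from its stated inputs, and the 96%/84% power ignores that only three facilities are randomised per arm

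*Protocol article*

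**What the plan says.** All references are to the protocol article.

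- Power, HCF: "We anticipate 300 workers from 6 facilities". The next sentence reads "Assuming the minimum number of 30 workers in each facility and ICC of 0.01, a design effect of 1.36 is expected", followed by "We anticipate 96% and 84% powers to detect the medium effect sizes of 0.5 and 0.4 for the difference in outcomes between the two interventions". The paragraph closes by judging both samples, YGBMSM and HCW, large enough for medium effects.
- Abstract, Methodology: "we will randomly assign 6 healthcare facilities (HCFs) to receive the LAFIYA (n=3) or wait-list control (n=3").
- Randomization, under HCF: "we will first stratify 6 HCFs into groups of two, larger, medium, and smaller sizes", with one facility of each stratum going to each arm.
- Data analysis, under Appraisal of intervention: one paragraph covers all quantitative outcomes. Its longitudinal model is a "generalized linear mixed effect model (GLMM) with random intercept and peer group, which incorporate ICCs". No facility term is named.
- Power, YGBMSM: for comparison, an ICC of 0.04 with 8 people per friend group is said to give a design effect of 1.28, at a 5% significance level.

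**The concern.** Two things look wrong in the HCF power paragraph. The cluster size, ICC and design effect stand in one sentence but do not fit together, and the total of 300 workers implies a third, different cluster size. Separately, the comparison is between three facilities and three facilities, yet the power is as high as if about 110 independent people per arm were compared. A design effect corrects the variance for clustering. It does not correct for how poorly between-facility variance is estimated from six facilities.

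The secondary hypothesis in Step 8 includes a reduction in the stigma and discrimination that facility staff convey. If that comparison is presented as well powered when it is not, a null result may be read as evidence of no effect. The article says the findings will be used to finalise an efficacy trial protocol, so the misreading would carry forward. The analysis text adds a related risk: its one named cluster term is the peer group, a YGBMSM friendship unit that HCWs do not have.

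**Working it through.** **Inputs.** 300 workers, 6 facilities, a minimum of 30 per facility, ICC 0.01, effects 0.5 and 0.4 SD (Power, HCF). Three facilities per arm (Abstract; HCF Randomization). Alpha 5% is stated only for the YGBMSM calculation; it is assumed to apply here too, two-sided.

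**1. Design effect.** DE = 1 + (m − 1) × ICC. This reproduces the friend-group figure: 1 + 7 × 0.04 = 1.28. For HCWs at ICC 0.01:

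- m = 30: 1 + 29 × 0.01 = 1.29
- m = 300/6 = 50: 1 + 49 × 0.01 = 1.49
- DE 1.36 requires m = 0.36/0.01 + 1 = 37, or ICC = 0.36/29 = 0.0124 at m = 30, or ICC = 0.36/49 = 0.0073 at m = 50. None of these is stated.

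Unequal facility sizes do not rescue 1.36, because with a mean of 50 they push the DE above 1.49. With an assumed split of 30, 50 and 70 (two facilities each), DE = 1 + (16,600/300 − 1) × 0.01 = 1.54.

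**2. Reproducing the stated power.** Effective n per arm = 150/1.36 = 110.3. Noncentrality = d × √(n/2) = 3.71 (d = 0.5) and 2.97 (d = 0.4). Against the normal critical value 1.96, power is 96.0% and 84.4%; a t-test with person-level df gives 95.9% and 84.1%. The stated 96%/84% therefore comes from N = 300, DE 1.36 and a critical value based on individuals.

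**3. Correcting the DE only.** Effective n = 150/1.49 = 100.7; noncentrality 3.55 and 2.84; normal-approximation power 94.4% and 81.0%.

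**4. Using the unit of randomisation.** Six facilities in two arms leave 6 − 2 = 4 df, so the critical value is 2.776. Power from the noncentral t distribution:

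| DE | df | d = 0.5 | d = 0.4 |
|---|---|---|---|
| 1.36 (as stated) | person-level | 96% | 84% |
| 1.49 | person-level (normal) | 94.4% | 81.0% |
| 1.36 | 4 | 79.1% | 61.1% |
| 1.49 | 4 | 75.6% | 57.4% |
| 1.49 | 2 (three pairs, no variance removed) | 48.6% | 35.9% |

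Simulating a t-test on six facility means (50 workers each, ICC 0.01) gave 75.8% and 57.5%, in agreement with the 4-df row.

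**5. If facility were left out of the HCW model.** The nominal 5% test would have an error rate of about 2 × [1 − Φ(1.96/√1.49)] = 2 × [1 − Φ(1.606)] ≈ 0.108, or about 11%, at the protocol's own ICC.

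**The case against.** The strongest reply has four parts.

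- *The DE slip changes nothing of substance.* This stands: at 1.49 both powers stay above 80% by the protocol's own method. The finding rests on the facility-level df.
- *The 76%/57% is conditional.* This also stands. It assumes equal facilities and a single unadjusted comparison, while the article plans a baseline and three follow-up surveys in a longitudinal model. For illustration, with an assumed baseline–outcome correlation of 0.5 at both levels, the variance factor is 1 − 0.25 = 0.75 and power with 4 df is about 86% and 69% (77% and 60% if the covariate costs one df). The article gives no correlation and its power paragraph claims no such gain.
- *The analysis paragraph is condensed and writes no separate HCW model.* It speaks of ICCs in the plural, after a power section with one ICC for friend groups and another for facilities. A reader might infer that the plan ignores facility clustering and so doubles the false-positive rate. The text does not establish that; the 11% holds only if the facility term is really omitted.
- *The outcome is secondary and the trial is a pilot of preliminary efficacy.* This lowers the severity. It does not excuse the figures, because the paragraph makes an explicit power claim.

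A reader might also infer that no result can be significant. The paired randomisation allows 2³ = 8 allocations, so an exact randomisation test could not give a two-sided p below 2/8 = 0.25. No such test and no pair-matched analysis is specified, so neither that floor nor the 2-df power follows from the written plan.

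**Conclusion.** The HCW power paragraph is wrong as written. The design effect of 1.36 contradicts both cluster sizes in the same paragraph, with small effect. The stated power takes no account of three facilities per arm, with a material effect: about 76% instead of 96% at 0.5 SD, and about 57% instead of 84% at 0.4 SD, a loss of some 20 and 27 points. This rests on ICC 0.01, 50 workers in each facility, two-sided 5% alpha, no attrition and one unadjusted comparison of means. Baseline adjustment could raise power by an amount the article gives no means to compute; a pair-matched analysis could lower it. Under these assumptions the conclusion that 300 HCWs suffice for medium effects is not supported.

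The modelling point holds only as a need to specify the HCW cluster term. The YGBMSM power calculation for the primary hypothesis is untouched. Severity: should fix.

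**What to change.** - **Power, HCF.** Reconcile the minimum of 30 with 300/6 = 50, state the expected facility sizes, and restate the design effect (1.49 if facilities are equal; about 1.54 under a 30/50/70 split).
- **Same paragraph.** Restate power with facility-level df, about 76% and 57% under the assumptions listed. Say that baseline adjustment could raise it, and that a pair-matched analysis on 2 df would lower it (about 49% and 36% if pairing removes no variance). Withdraw or qualify the closing statement that the HCW sample is sufficient.
- **Data analysis.** For HCW outcomes, specify a facility random effect with small-sample df, or an analysis of the six facility means.
- **Reporting.** Give the HCW effect with a facility-level confidence interval.

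The cost is a rewritten paragraph, one model term and a less favourable stated power. No extra participants are needed and the randomisation is unchanged.

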### Implementation of the intervention

#### Implementation procedure.

The facilitators trained in aim one will receive a copy of the manual on delivering each component of the adapted intervention. The intervention will be participatory.

#### YGBMSM:

The implementation partners will recruit the YGBMSM to attend a 3-day weekend retreat at a location they identified with support from the site PI and Contact PI. Considering that YGBMSM remain hidden, we expect to utilize places we used in previous interventions^3,5,8,9,33^. Such locations have already been appraised and assured security. YGBMSM, who accept to participate in the intervention, will receive retreat dates. Participants will attend an orientation to obtain information about the retreat’s logistics and format and establish ground rules for appropriate behavior.

#### Criteria:

The person must be between 18 to 25 years old, currently identifies as a cis-gender man, have had sex with another man within 8 months before engaging with the recruitment team, and must reside within a slum in the Accra metropolitan area. **Randomization**. When we complete the recruitment and baseline survey, we will stratify peer groups by the number of peer members and give a group ID to each peer group. Within each stratum with an equal number of peers, we will randomly select groups for intervention using simple random sampling. Thus, we will keep equal samples and peer groups between the two study arms.

#### HCF:

The participatory exercises in this intervention will be delivered over two days to groups of 15 to 25 HCWs mixed by department and level (clinical/non-clinical) arranged based on the schedule of workers to ensure facility services are not disrupted.The team will work with management to assign people to the intervention before or after their shift. We used this process in our previous studies and successfully implemented the testing intervention across 8 facilities and over 1000 participants^34,73,74,81,98^

#### Randomization.

We will assign 3 HCFs to intervention or control groups based on size; we will first stratify 6 HCFs into groups of two, larger, medium, and smaller sizes, and assign one from each stratum to either arm using SRS.

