### Study setting.

Accra, Ghana, the proposed study area, remains the primate city in Ghana, housing over 5 million people and about half of the urban population, 38% in Ghana^76–78^. Like other large cosmopolitan areas in SSA, Accra has the highest concentrations of slum communities, with half its population living in about 80 slums. About 20% of housing in Accra has an incomplete roof, yet 75% of such houses have inhabitants. About 32% of all housing in Accra consists of non-conventional structures (e.g., metal containers, wooden structures, kiosks)^78,79^. Accra also has the highest prevalence of HIV among SMM (44%) and part of the highest among the general population (3%), which is higher than the nations (2%)^80^.

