### STEP 8 (Testing/Aim 2): Test the preliminary efficacy of the intervention to address ISD and increase HPART adherence using CRT Design

We will pilot-test the *LAFIYA* multilevel intervention using a clustered randomized control trial (CRT) with 9 months of waitlist control. Our ultimate aim is to adapt the intervention and preliminary test it for future full-efficacy CRT ^118,119^. Although RCT is primarily used in HIV and behavioral interventions, we find CRT better due to our place-based focus and possible sample contamination. In our previous single arm-pilot (2P30MH062294 −20 // Yale #18–001890, PI, [name]), we identified group sleeping arrangements, observed close-knit networks of GBMSM, and the communal nature of slums as contaminants. We will create two pairs of facilities matched by size and location in each city and randomly assign them to receive the LAFIYA-HCF intervention or the control group. Based on friendship networks, we will create GBMSM groups of 5 to 8 members and randomly assign YGBMSM groups to the LAFIYA-YGBMSM intervention or control group. YGBMSM in the intervention group will be matched with intervention HCF for status-neutral services. The YGBMSM in the waitlist control group will be matched with HCFs in the waitlist control for regular testing, PrEP, and care services. Nurses from the intervention HCF will participate as guest facilitators in one of the LAFIYA-GBMSM sessions. They will use that opportunity to contact YGBMSM to visit their facility for status-neutral care. We will collect 3, 6, and 9 months post-intervention data to measure the preliminary efficacy of the intervention and then implement the intervention in the waitlist group after the completion of data collection. We will use 9 months instead of 6 to allow ample time to measure multiple components, **such as viral suppression,** over a sufficient time. **Our primary hypothesis** is that LAFIYA will increase adherence to HPART among YGBMSM participants. **Our secondary hypothesis** is that the multilevel intervention will reduce the ISD that HCF staff convey and YGBMSM experience in HCFs. It will build the HCF’s capacity to implement status neutrality. We will then **conduct a follow-up qualitative study** (FGDs and IDIs) post-intervention among implementers and participants to evaluate their experiences with the intervention and to seek a more profound understanding or explanations for some of the survey findings.

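### The article's two facility allocation rules conflict on location and friend groups have no location factor, so access to the assigned facility can differ between arms by chance

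*Protocol article*

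**What the plan says.** The article randomises at two levels and then links them.

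- **Facilities, design text (STEP 8, Testing/Aim 2).** Facilities are to be formed into "pairs of facilities matched by size and location", two pairs in each city, and randomised.
- **Facilities, implementation text (Randomization, under HCF).** The rule here is "We will assign 3 HCFs to intervention or control groups based on size". To do so, "we will first stratify 6 HCFs into groups of two, larger, medium, and smaller sizes", and one facility of each stratum goes to each arm. Location is not mentioned.
- **Friend groups (Criteria, under YGBMSM).** An eligible man "must reside within a slum in the Accra metropolitan area". No link to a study facility is required. The Study setting section describes Accra as a city "with half its population living in about 80 slums". For allocation, "we will stratify peer groups by the number of peer members"; no other factor is named. Groups are randomised after the baseline survey.
- **The link between levels (STEP 8).** "YGBMSM in the intervention group will be matched with intervention HCF for status-neutral services". Control men are likewise matched with control facilities.
- **Analysis (Data analysis, under Appraisal of intervention).** The mixed model has a random intercept and a peer-group effect. Demographics found to be non-equivalent between arms are added as covariates. No facility or location term is named.
- **Baseline data (Measures).** Neighborhood, and access to and use of health services, are recorded for description.

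**The concern.** The two facility rules cannot both be followed, and they differ on the one factor, location, that bears on how easily a man can reach the facility of his arm. Nothing at friend-group level makes up for this, because groups from anywhere in the metropolitan area are balanced on size alone.

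Testing, PrEP and ART outcomes are at stake. PrEP and ART services are delivered through the facility matched to the arm, and the Data collection section has the facilities supply the PrEP and ART adherence biomarkers at routine visits. The team's own earlier interviews list location and cost among the barriers to testing (Preliminary Studies, Testing/self-testing). If one arm's facilities happen to be easier for its men to reach, part of an observed difference could reflect access. All men in an arm share three facilities, so enrolling more men does not average out a difference between facilities.

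**Working it through.** **1. Does each facility rule give six facilities?**
- Planned number: 6, three per arm (Abstract; Power, HCF; Randomization, HCF).
- STEP 8 rule, one city: 2 pairs × 2 facilities = 4. Two cities: 2 × 2 × 2 = 8. Neither gives 6, and Study setting names Accra alone.
- Randomization rule: 3 strata × 2 facilities = 6. This fits, but drops location.

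**2. Does the plan's own figure touch the point?** Inputs from Power, YGBMSM: 120 per arm, ICC 0.04, groups of 8, effect size 0.50, 5% level (taken as two-sided).
- Design effect = 1 + (8 − 1) × 0.04 = 1.28, as stated.
- Effective n per arm = 120 / 1.28 = 93.75.
- 0.50 × √(93.75 / 2) − 1.96 = 3.42 − 1.96 = 1.46, so power is 92.8%, against 92.7% stated.

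The figure reproduces. It allows for friend-group clustering only and says nothing about location. No stated number is wrong on this point.

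**3. How uneven could facility location be under size-only pairs?** The article gives no map, so this is an illustration. Assume three facilities in area A, three in area B, and area unrelated to size.
- Chance that all three intervention facilities are in A = 1 / C(6,3) = 1/20 = 5%; the same for all three in B. Together 10%.
- Chance of a 2:1 or 1:2 split = 18/20 = 90%.
- An even split cannot occur with three facilities per arm. That is arithmetic, not a fault of the rule.
- For a continuous facility feature such as average travel time, the SD of the arm difference is √(1/3 + 1/3) = 0.82 between-facility SDs.

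Pairing on location under the same assumption gives one A pair, one B pair and one mixed pair, so the split is always 2:1 or 1:2 and the 10% case disappears. If the six facilities instead lay two in each of three areas, location pairs would put one facility per area in each arm.

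**4. How uneven could friend-group location be?** Power gives about 15 groups per arm. Assume groups come half from each of two areas.
- SD of the arm difference in area share = √(0.5 × 0.5 × 2 / 15) = 0.18, about 18 percentage points.

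This second source remains even if the location-matched facility rule is the one that governs.

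**5. What would a location factor cost in strata?** Groups of 5 to 8 stratified by exact size make 4 strata. Two size bands × two areas is also 4. Two size bands × three areas is 6, or about 30 / 6 = 5 groups per stratum.

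**The case against.** Several points on the other side are sound.

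- **Location is not ignored.** A reader of the Randomization paragraph alone might infer that facility allocation takes no account of location. STEP 8 says otherwise, and the shorter paragraph may simply condense it. The supportable finding is a contradiction, together with the missing location factor for friend groups.
- **There is no systematic bias.** Facilities and groups are both randomised, so access is balanced in expectation. The risk is chance imbalance with few units.
- **It is not shown that distance governs uptake.** A reader might infer that a nearer clinic means more uptake, or that access could never be told apart from the intervention. No distances are given, and the article's own evidence is mixed. All 15 interviewees lacked confidence in testing at slum facilities, many men prefer to travel elsewhere or self-treat, and fear of being seen at HIV facilities is a reported barrier. Self-testing needs no clinic visit. The matching is not said to be exclusive, and how men are spread over their arm's three facilities is not described.
- **A probability that one arm gets all the better-placed facilities cannot be given.** It depends entirely on the assumed geography. The 10% above is one illustration.
- **Partial remedies exist.** Neighborhood is recorded before randomisation, non-equivalent demographics are adjusted for, and models are repeated by site. But distance is not named, the adjustment is triggered by the data, and separate site models do not balance or adjust the main comparison.
- **This is a pilot of preliminary efficacy.** That lowers the stakes, but its results are meant to shape the full trial.

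These points limit the finding to chance imbalance of unknown consequence. They do not remove the conflict between the two rules or the lack of a location factor for friend groups.

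**Conclusion.** The concern holds in a limited form. The article gives two incompatible facility rules: one uses location but cannot produce six facilities, and the other produces six but omits location. Friend groups from across the metropolitan area are stratified by size only and tied by arm to three facilities, and the model carries no facility or location term. Access to the assigned facility can therefore differ between arms by chance.

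On assumed geographies the imbalance could be appreciable: an SD of about 18 percentage points in area share between arms, and 0.82 between-facility SDs in a facility feature. These rest on two equal areas, location unrelated to size, and 15 groups per arm. Any effect on uptake is unknown. The document does not support a claim of systematic bias or of an access effect that determines the result.

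**What to change.** Recruitment has not begun (Trail Status), so the changes can be made in the allocation procedure.

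1. Replace the two facility rules with one for six facilities: three pairs formed on location as well as size, as far as six facilities allow, with one of each pair randomised to each arm.
2. Use the neighborhood already recorded at baseline, grouped into two or three areas, as a stratification factor for friend groups. Collapse group size to two bands (5–6 and 7–8) to keep strata few.
3. Include the same area variable as a prespecified covariate in the mixed model, whether or not a baseline difference appears.

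**Cost.** No new data item is needed. With four to six strata for about 30 groups, group counts may differ slightly between arms, which loosens the stated aim of equal arms. Six facilities may not match well on both factors. Pairing on location also brings facilities of opposite arms closer together, which must be weighed against the contamination that led the team to cluster randomisation. For that reason the proposal stops at a coarse area factor and does not tie every friend group to its nearest facility pair.
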